## Abstract

**Background:**

First-line therapy for patients with clinically relevant obstructive sleep apnoea (OSA) is positive airway pressure therapy (PAP). At least one half of patients with mild to moderate OSA (apnoea-hypopnoea-index (AHI) 5-30/h) have positional OSA (POSA), where apnoea occurs mostly in supine sleep. These patients might benefit from sleep-position therapy (SPT) which should reduce sleeping time spent in a supine position. Until now, it is unclear whether SPT is non-inferior to PAP therapy for symptom relief in these patients.

**Methods:**

This is a multicentre, non-inferiority, open-label randomised, cross-over clinical trial. Patients with mild to moderate POSA and daytime sleepiness (according to Epworth Sleepiness Scale (ESS) > 10 points) will be randomised with a 1:1 allocation ratio, stratified by centre and AHI, to start with either PAP therapy or SPT and treated for 12 weeks. After a wash-out period of two weeks, they will switch to the other therapy for 12 weeks. The primary outcome is daytime sleepiness measured by the ESS at the end of each treatment phase. Analysis will be done in the intention-to-treat population using a linear mixed-effects model containing the intervention, the phase, the interaction between therapy and phase (including the carry-over effect) and the baseline measurement of the ESS and AHI as fixed effect, and centre and patient as random effects. A one-sided test at significant level of 2.5% will be used to test the non-inferiority of SPT with a non-inferiority margin of 1.35. Based on a sample size calculation with a one-sided one-sample t-test at significant level of 2.5%, assuming a standard deviation of 4, a total of 418 patients should be included to reach 80% power when SPT is only slightly inferior to PAP therapy (difference 0.8 resulting in a delta of 0.55 (1.35-0.8)). Assuming a 5% drop-out rate, 220 patients per sequence should be included. Possible futility stopping is planned at an interim analysis after 300 patients.

**Discussion:**

The recruitment of patients with mild to moderate POSA is feasible with the planned centres. Both certified interventions (PAP and SPT) are covered by the statutory health insurance companies as part of the trial guideline.

**Trial registration:**

DRKS00033048 registered 17. June 2024, http://www.drks.de.

Role of sponsor {5c}	The trial has been commissioned by the German Federal Joint Committee (G-BA) to generate sufficient evidence for or against the reimbursement of sleep position therapy by the statutory health insurance funds in Germany. The G-BA has developed a draft study design (see “Erprobungsrichtlinie”). The study team led by the University of Duisburg-Essen, who acted as sponsor, applied for the call for bids and was awarded the contract. The sponsor and the study team are responsible for the conduct of the study, in particular the selection of the study centres, data collection, management of the study, statistical analysis, interpretation of the data and writing the report. In particular, the study team finalised the study protocol with all details. The final German-language study protocol was approved by the G-BA. The study team must regularly report the status of the trial to the G-BA. The final study report has to be approved by the G-BA

## Introduction

### Background and rationale {6a}

Obstructive sleep apnoea (OSA) is the most common organic sleep disorder. During sleep, the relaxation of the muscles leads to a narrowing or collapse of the upper airways. In addition to the occurrence of snoring, this is accompanied by restricted or interrupted ventilation of the lungs. These events are called hypopnoea and apnoea. The associated oxygen drops in the blood lead to short arousals and thus to an interruption of sleep. Even if the arousals are often not remembered the next day, around 1/3 of OSA patients report relevant daytime sleepiness. Subjective daytime sleepiness can be determined using internationally validated questionnaires such as the Epworth Sleepiness Scale (ESS) [1]. In the medium to long term, the stress reactions caused by sleep-related breathing disorder also led to an increased risk of cardiovascular diseases, depression, and dementia [2]. After a specific medical history, patients with suspected OSA get an overnight portable breathing monitoring system (polygraphy = PG) at their homes in accordance with the German guideline on methods of contract medical care issued by the German Federal Joint Committee (G-BA) [3]. If there is a hint of a sleep-related breathing disorder, but a final diagnosis cannot be proven based on portable monitoring, the diagnosis is confirmed by a fully attended polysomnography (PSG) in a sleep laboratory.

The severity of OSA is defined by the apnoea-hypopnoea index (AHI)—i.e. the number of breathing disturbances per hour of sleep. Here, the normal value is an AHI < 5/h. A mild OSA is diagnosed with an AHI of 5– < 15/h, a moderate OSA with an AHI of 15– < 30/h, and a severe OSA with an AHI ≥ 30/h. Based on the AHI, current epidemiological studies show a high prevalence of OSA. In Germany, for example, around 14 million people are estimated to show an AHI ≥ 15/h and even around 26 million an AHI ≥ 5/h [4]. According to the S3 guideline of the German Society for Sleep Research and Sleep Medicine (DGSM), treatment is indicated for an AHI ≥ 15/h regardless of the associated symptoms or for mild OSA (AHI 5– < 15/h) with associated symptoms or an increased cardiovascular risk due to existing comorbidities [5].

The first-line therapy is positive airway pressure (PAP) therapy at night. During sleep, positive air pressure is delivered to the upper airways via a nasal or oronasal mask to keep them open. This effectively prevents obstructive sleep-related breathing disorders. This not only has a positive effect on daytime sleepiness, but also on the increased long-term risk of subsequent diseases. In line with the guideline, PAP therapy is initiated during a fully attended PSG in a sleep laboratory. This involves finding the optimum pressure setting that can keep the airways open. In most cases, a pressure range is set; the therapy device then automatically adjusts the necessary therapy pressure to the patient's needs during the night (automatic PAP therapy = APAP).

At least one half of patients with mild to moderate OSA have positional OSA, where apnea occurs mostly in supine sleep. In relation to the overall AHI averaged over the night, which shows a mild to moderate degree of OSA, the index in supine position is at least twice as high compared to the AHI in non-supine position [6]. Studies have shown that preventing supine sleep by means of sleep position therapy (SPT) can lead to a significant reduction in the overall AHI [7]. For example, SPT can be carried out using a position sensor, which is attached to the sleeper with an abdominal belt and in case of supine position uses gentle vibrations to encourage a change of position. Initially, sleep can be interrupted by this, so that a familiarisation phase of up to 4 weeks is assumed. During this time, a conditioning effect occurs, which should lead to avoidance of the supine position at night. Studies confirm the effect of such a therapy in terms of reducing sleep-related breathing disorders, but the effects on endpoints such as daytime sleepiness are not conclusively compared to established PAP therapy [6].

### Objectives {7}

The POSA trial is intended to answer the open question, whether SPT is at least as good as PAP therapy to reduce daytime sleepiness after 12 weeks of treatment in patients with mild to moderate positional OSA complaining relevant sleepiness assessed by Epworth-Sleepiness-Score > 10 points.

### Trial design {8}

This is a multicentre, individually randomised, controlled, non-inferiority trial with a cross-over design. Patients are randomised (1:1) to start with either PAP therapy or SPT and are treated for 12 weeks. After a subsequent wash-out period of 2 weeks, the study participants switch therapy groups and are treated with the other therapy for 12 weeks (see Fig. 1). Hence, there are two groups with different treatment sequences (1) SPT → PAP and (2) PAP → SPT. The length of the wash-out period was chosen based on recently published studies, in which the duration of this phase was only 0 or 1 week and yet there was no carry-over effect [6].

**Fig. 1 Fig1:**
[figure not shown]
Study flow for the patients

## Methods: participants, interventions and outcomes

### Study setting {9}

The study participants are recruited by specialists in sleep medicine or somnology in Germany. Patients who are referred to a sleep laboratory for diagnostic confirmation in case of suspected OSA according to clinical routine are screened for eligibility criteria. Based on the diagnostic polysomnography performed, the inclusion and exclusion criteria are checked by the investigators at the respective study centre. Furthermore, the medical devices for the interventions are given to the patients and are used at home.

### Eligibility criteria {10}

In order to participate in the trial, the following requirements should be met by the study centres. The study centres should be specialised in patients with sleep-related breathing disorders and must have access to a clinical sleep laboratory to perform fully attended polysomnography. In addition to qualified study personnel in accordance with GCP, a study physician with additional qualifications in sleep medicine or somnology who has experience in clinical sleep medicine studies should be on site. This ensures a high-quality study implementation in accordance with the protocol. It should also preferably be an outpatient sleep laboratory, as the patient population addressed is more likely to be expected and thus recruited in the outpatient care sector due to the inclusion and exclusion criteria.

Potential study participants are patients who are referred to a sleep laboratory for diagnostic confirmation of suspected OSA according to clinical routine and existing guidelines. Based on the diagnostic polysomnography performed, the following inclusion and exclusion criteria are checked by the investigators of the respective study centre. To ensure high quality, from each study centre up to five randomly selected PSG from the first inclusion nights should be verified by the Core Lab (Centre for Sleep and Telemedicine, University Medicine Essen). In the event of major deviations, the centre staff is trained by employees of the Core Lab.

Inclusion criteria:

Adult patients with age ≥ 18 yearsMild to moderate, supine-dependent obstructive sleep apnoea (total apnoea-hypopnoea index (AHI): 5– < 30/hAt least twice as high AHI in supine position compared to non-supine positionAt least 30% of total sleep time in supine positionAHI in non-supine position: < 10/h)Indication for nocturnal positive airway pressure therapy with relevant daytime sleepiness (Epworth Sleepiness Scale (ESS) > 10 points)

Exclusion criteria:

Previous or ongoing sleep apnoea therapy using equipment or surgeryExisting oxygen therapyActive professional activity as a professional driverExisting pregnancyTaking sedative or vigilance-enhancing medicationUnstable medical condition which, in the opinion of the investigator, impairs participation in the studyPresence of other relevant sleep disorders affecting daytime sleepinessExcessive alcohol consumption (> 3 drinks/day)Drug useSevere claustrophobiaMusculoskeletal problems that restrict sleeping in the lateral positionInability to understand the study and patient information leafletPatients with an active cardiac device (pacemaker, AICD, CRT, etc.)Use of other medical devices (e.g. implanted aggregates, neurostimulation procedures, etc.) that could be affected by the light vibration stimuli on the chest caused by the sleep position trainerHealth condition that requires sleeping in a supine position (e.g. due to shoulder or back surgery or osteoarthritis)Upright sleeping position (e.g. by using more than two pillows)

### Who will take informed consent? {26a}

Based on the patient’s medical history and clinical findings (ESS score, ambulatory polygraphy findings), the eligibility of the patient for the study is determined by the study physician with additional qualifications in sleep medicine or somnology on site before the diagnostic PSG (first PSG in Fig. 1). If the patient is eligible for participation in the study based on these criteria, they will be informed about the study. As part of the information, the study is explained in detail regarding the background, the study design, the devices, the assessments, the handling of the participants’ data and the potential benefits for the participants. The investigators then obtain verbal and written consent from the study participants at the latest after the diagnostic PSG.

### Additional consent provisions for collection and use of participant data and biological specimens {26b}

Not applicable.

## Interventions

### Explanation for the choice of comparators {6b}

The first-line therapy for clinically relevant OSA is PAP therapy during sleep. PAP therapy is initiated in line with national guidelines during a fully attended polysomnography in a sleep lab. This involves finding the optimum pressure setting that can keep the airways open. In most cases, a pressure range is set; the therapy device then automatically adjusts the necessary therapy pressure (APAP) to the patient’s needs during the night. Once the optimal pressure range is set at the beginning of the 12-week period during sleep lab stay, it typically remains unchanged throughout the intervention phase. The APAP device continuously adjusts the delivered pressure within this predefined range in response to detected obstructive events during sleep (e.g. flow limitation, snoring, apnoeas, hypopnoeas). There is generally no routine adjustment of the pressure range by clinicians unless there are specific clinical concerns (such as insufficient treatment response or patient-reported side effects) prompting a reassessment. In our study, no protocolised or systematic re-titration or range adjustments were scheduled during the 12-week intervention.

### Intervention description {11a}

In SPT, a sensor is attached to the body via an abdominal belt: in case of sleeping in the supine position, SPT emits gentle vibrations that prompt the patient to change their sleeping position without disturbing their sleep. After the tenth night, when the vibration level has been gradually increased to reach the target stimulus intensity, this level remains constant during the remaining intervention period. The device continues to deliver vibrations at this intensity whenever the patient moves into the supine position. Similar to the APAP arm, no scheduled adjustments were made during the 12-week phase– especially as the stimulation settings cannot be changed with the SPTs used. The SPT is a certified medical product and begins by analysing sleep during the first two nights. From the third and up to the tenth night, light vibrations are then gradually increased to help the patient get used to the SPT device. The SPT mobile app allows the course of therapy to be tracked and accessed at any time.

### Criteria for discontinuing or modifying allocated interventions {11b}

Patients can withdraw their informed consent at any time without explanation. If the patient withdraws consent, no further data will be collected. The data already collected until that point will be stored and used for study purposes, if the participant does not request the deletion of their data. Data that has already been collected and included in analyses at the time of the request for data deletion remains unaffected by the deletion.

In case of proven failure of the above inclusion and exclusion criteria at baseline, the study participant may no longer participate in the study. This also applies if one of the exclusion criteria occurs during the course of the trial.

Study participants have the option to discontinue the intervention at any time without explanation. If a participant wishes to discontinue intervention, this is noted in the eCRF by the study staff, and the participant is asked for the reasons. In addition, the intervention can be discontinued by the attending physician in the event of intolerance of the intervention confirmed by the attending physician. Participants who discontinue intervention can continue to take part in the study and are then documented according to the protocol. They remain within the specified time schedule, i.e., in the event of a discontinuation of intervention during the 1 st intervention phase, the T1 and T2 visits take place at the specified times and, if desired, a cross-over to the respective comparative intervention in the 2nd intervention phase.

### Strategies to improve adherence to interventions {11c}

During the intervention phases, patients in both groups are contacted at one, two, four and eight weeks after intervention start to remind them to use the therapy regularly. To monitor adherence to the therapy, usage data of SPT or PAP therapy will be read out from the devices. The app of the respective device is used for this purpose, in which the data is saved regularly and can then be read out at the end of the delivery period.

### Relevant concomitant care permitted or prohibited during the trial {11d}

No other therapies for OSA are permitted.

### Provisions for post-trial care {30}

After the participants complete the trial, they will receive standard treatment according to the national guidelines, which is currently PAP therapy.

## Outcomes {12}

The primary endpoint of the study is the change in subjective daytime sleepiness, measured with the ESS [1] before and 12 weeks after the start of the respective intervention. The following parameters are to be analysed as secondary endpoints:

Subjective sleep quality according to the Pittsburgh Sleep Quality Index (PSQI) [8]Objective sleep parameters derived from PSG in comparison to the initial diagnostic PSG-examination: Total AHI, proportion of sleep time in supine position, AHI in supine position, AHI in non-supine position, oxygen desaturation index (ODI), mean oxygen saturation (SaO2 mean), minimum oxygen saturation (SaO2 min), time with oxygen saturation < 90% (T90) (all assessed by pulse oximetry), Total sleep time (TST), sleep onset latency, total wake time after first falling asleep (WASO), sleep efficiency (SE), sleep times in sleep stages N1, N2, N3 and REM, heart rate variability, arousal index, respiratory disturbance index (RDI) [9]Health-related quality of life according to the Functional Outcomes of Sleep Questionnaire (FOSQ-10) [10]Quality of life according to EuroQol-5D-5L (EQ-5D-5L) [11]Adverse events (AEs) according to standardised severity classification and treatment discontinuations due to AEsUsage data of SPT or PAP therapy to evaluate therapy adherence and to analyse a usage-related therapy effect (here: daytime sleepiness), as sufficient and regular use of sleep apnoea therapy is a prerequisite for the therapy effect in relation to the baseline. For this purpose, a corresponding effectiveness analysis should be carried out (analysis of the actual utilisation time of the respective intervention in relation to the mean, specified total sleep time in the corresponding intervention phase). The utilisation data can be read out easily and securely via the SPT device application or via the PAP device’s internal data stored on a SD card or transmitted by telemonitoring.

### Participant timeline {13}

To screen patients, the ESS is assessed, and an initial polysomnography is performed. If a patient fulfils the inclusion criteria, informend consent is obtained, and all other assessments will be performed as given in Table 1. Further visits to the study centres are scheduled at the end of each therapy phase and at the beginning of the second therapy phase for the assessment of the endpoints (Table 1).

**Table 1 Tab1:**
[figure not shown]
Schedule and timing of planned assessments

*At week 1, 2, 4, and 8 after T0 and at week 1, 2, 4, and 8 after T2; **only for controlled initiation of PAP therapy; ^#^additional assessments during reminder contacts

### Sample size {14}

The aim of the study is to show that SPT is not inferior to PAP therapy in terms of daytime sleepiness measured with the ESS. A difference of 1.35 between the two means is proposed as the non-inferiority threshold, i.e. the hypothesis pair:$$H_0:\mu_{SPT}-\mu_{CPAP}\geq1.35\;vs.\;H_1:\mu_{SPT}-\mu_{CPAP}<1.35$$should be tested with a one-sided test at significance level of 2.5%.

This means that under the alternative hypothesis, the ESS value measured under SPT may not be more than 1.35 points higher on average than the ESS value under PAP therapy. The choice of the value for the non-inferiority margin is justified as follows: The study by Crook et al. investigated the size of the clinically relevant difference for the ESS. Depending on the method used, the difference was between 1 and 4.21 [12]. In other non-inferiority studies, a difference of 1.5 or 2 points was often chosen as the non-inferiority threshold [13]. One meta-analysis showed a difference between PAP vs. no therapy of 2.4 points (95% CI, 1.9 to 2.8) [14]. However, a more recent meta-analysis showed that this difference depends, among other things, on the baseline ESS and AHI. For example, a difference of 1.34 (0.68 to 1.99) was found for a baseline ESS > 10 points and AHI 5 to < 15/h and 2.22 (2.13 to 2.30) for an AHI 15/h to < 30/h [15]. Therefore, the size of the non-inferiority margin of 1.35 provided in the documents of Federal Joint Committee seemed appropriate to ensure at least a difference compared to no therapy in the planned study population.

Hence, sample size calculation was done using a one-sided one-sample *t*-test at a significance level of 2.5% and to achieve a power of 80% to test the above hypotheses. It was assumed that the difference between SPT and PAP is 0.8 points. Sample size calculation for a δ of 0.55 points (1.35–0.8), assuming a standard deviation of 4, results in a required sample size of 418 patients in total, i.e. 209 per sequence. A drop-out rate of 5% is assumed according to the studies by Berry and Mok, i.e. revocation or completely missing data after baseline [6, 13]. Therefore, a total of 440 patients, i.e. 220 per sequence, will be recruited into the study. Further missing values do not affect the sample size, as they will be replaced according to the analysis strategy.

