### Methods for additional analyses (e.g. subgroup analyses) {20b}

The following subgroups should be considered: Mild OSA (AHI 5– < 15) vs. moderate OSA (AHI 15– < 30). The analyses in the subgroups are performed analogously to the analyses of the overall population.

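### The 1.35-point margin is said to secure a benefit over no therapy, but the protocol's own PAP effect in mild patients (1.34, lower limit 0.68) gives no such assurance for the mild stratum

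*Protocol article*

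**What the plan says.** All the figures are in the protocol article, Sample size {14}. The margin is introduced there: "A difference of 1.35 between the two means is proposed as the non-inferiority threshold". It comes from the commissioning body's documents and is supported by several pieces of outside evidence: a range of clinically relevant ESS differences (1 to 4.21), margins of 1.5 or 2 points in other trials, and an overall PAP effect against no therapy of 2.4 (1.9 to 2.8).

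The section then notes that the PAP effect varies with baseline ESS and AHI. For mild disease, "a difference of 1.34 (0.68 to 1.99) was found for a baseline ESS > 10 points and AHI 5 to < 15/h". For AHI 15 to below 30/h it gives 2.22 (2.13 to 2.30). The next sentence concludes from this that the margin "seemed appropriate to ensure at least a difference compared to no therapy in the planned study population".

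The eligibility criteria admit total AHI from 5 to below 30/h and state no cap on mild patients. AHI class (mild or moderate) is a stratification factor in Sequence generation {16a}. It is also the planned subgroup in section {20b}, where "The analyses in the subgroups are performed analogously to the analyses of the overall population". The confirmatory test is on the pooled population.

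**The concern.** The trial has no untreated arm. A non-inferiority result can imply that SPT beats no therapy only if the margin is smaller than the PAP effect that can be relied on. To ensure this, the margin has to lie below the lower confidence limit of that effect, not merely near its estimate. In the mild stratum the protocol's own figure does not meet that condition, yet the conclusion is drawn for the whole planned population.

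The trial was commissioned to inform a reimbursement decision. A reader of a positive result who relies on the stated rationale would take it that SPT has been shown to work better than nothing, mild patients included. If the subgroup analysis is also judged against 1.35, a mild-subgroup result inside the margin invites the same reading.

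**Working it through.** **Inputs from Sample size {14}:** margin 1.35; one-sided 2.5% test; 80% power; assumed true difference 0.8; distance 0.55; SD 4; PAP against no therapy 1.34 (0.68 to 1.99) in mild and 2.22 (2.13 to 2.30) in moderate OSA. **Assumed, because not given:** the mild share *w*; 209 mild patients (half of 418) where a subgroup size is needed; SD 4 within the subgroup.

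**1. The plan's own figure.** For a one-sample t-test with distance 0.55 and SD 4, the smallest n with at least 80% power under the noncentral t distribution is 418 (power 80.1%). Allowing for 5% drop-out, 418/0.95 = 440. Both figures reproduce. The fault is in the margin's rationale, not in the sample size.

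**2. Margin against each quoted effect.**

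| PAP vs no therapy | Value | Margin / value | Value − margin |
|---|---|---|---|
| Mild, estimate | 1.34 | 101% | −0.01 |
| Mild, lower limit | 0.68 | 199% | −0.67 |
| Moderate, estimate | 2.22 | 61% | 0.87 |
| Moderate, lower limit | 2.13 | 63% | 0.78 |

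The margin fails in mild patients on both figures and holds in moderate patients on both.

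**3. Pooled population.** The mixed effect is 1.34*w* + 2.22(1 − *w*). It stays above 1.35 until *w* = (2.22 − 1.35)/(2.22 − 1.34) = 0.989.

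For the lower limit, SE(mild) = (1.99 − 0.68)/3.92 = 0.334 and SE(moderate) = (2.30 − 2.13)/3.92 = 0.043. The lower limit is the mixed effect minus 1.96 × √[(0.334*w*)² + (0.043(1 − *w*))²].

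| Mild share | Mixed effect | Lower 95% limit |
|---|---|---|
| 50% | 1.78 | 1.45 |
| 60% | 1.69 | 1.30 |
| 70% | 1.60 | 1.14 |

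The lower limit crosses 1.35 at about 57% mild. Averaging the two lower limits directly gives (2.13 − 1.35)/(2.13 − 0.68) = 54%.

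**4. A mild-only test at 1.35 with an inert SPT.** If SPT does nothing, the true SPT − PAP difference equals PAP's effect. With n = 209, SE = 4/√209 = 0.277, and the test passes for an observed difference up to 1.35 − 1.971 × 0.277 = 0.80. From the noncentral t distribution:

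- PAP's true mild effect 1.34 (distance 0.01): pass probability 2.7%; 2.8% with n = 418.
- PAP's true mild effect 0.68 (distance 0.67): pass probability 67%; 93% with n = 418.

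The force of the point therefore lies in the lower limit, not in the 0.01 excess at the estimate.

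**5. What an indirect comparison could show in mild patients.** Adding variances, SE = √(0.277² + 0.334²) = 0.434, so the 95% half-width is 1.96 × 0.434 = 0.85. An observed SPT − PAP of 0 gives an SPT effect over no therapy of 1.34 (0.49 to 2.19). An observed 0.8 gives 1.34 − 0.8 = 0.54 (−0.31 to 1.39). Both observed differences satisfy the 1.35 margin, since they do not exceed 0.80 (unrounded cut-off 0.8045), but only the first supports efficacy over no therapy.

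**The case against.** The strongest defence is that the sentence speaks of the planned population as a whole, which is mild to moderate, and that the test is pooled. At the quoted estimates the pooled PAP effect exceeds 1.35 up to about 99% mild. If SPT were inert in both classes, the trial would pass at most about 0.1% of the time for mild shares up to 75%. This stands: as a statement about the average at the point estimates, the rationale is defensible. It does not stand as an assurance, because it ignores the uncertainty in the mild figure and says nothing about the mild stratum itself.

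A reader might go further and infer that a positive trial is compatible with SPT doing nothing in mild patients, and treat this as a defect of the margin. It can happen: at 50% mild with a PAP effect of 1.34 there, the pooled trial passes 93% of the time if SPT equals PAP in moderate patients, but 30% if SPT is 0.8 worse there. Any pooled test allows this, however, and no pooled margin guarantees an effect in each class.

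A reader might also infer that passing 1.35 in mild patients carries no evidence at all. At a PAP effect of 1.34 that is wrong, since the error rate of 2.7% is close to the nominal 2.5%.

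Two further points stand. The subgroup section says only that the analyses are analogous; that 1.35 would serve as a subgroup criterion is an inference, and the SAP, which may settle it, is not at hand. The margin also has other support in the text and is stricter than the 1.5 or 2 points cited from other trials. The protocol sets no rule for the share of effect to be retained, so those percentages are not in themselves a breach.

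**Conclusion.** The concern holds in a limited form and should be fixed. The claimed assurance of a difference from no therapy contradicts the protocol's own figure for mild patients, a stratum enrolled without a stated cap. For the pooled population the claim is true on average at the point estimates, but it is not assured at the lower 95% limit above about 57% mild (54% by direct averaging of the limits). The mild share is unknown. The mixing calculation also takes the two quoted estimates as independent and as applying to this trial's patients.

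The documents do not support reading this as an invalid margin, a wrong sample size, or a pooled result that says nothing about efficacy. The point changes what a positive result may be said to show, chiefly in mild patients.

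**What to change.** Keep the 1.35 margin, the primary test and the sample size as they are. Before results are known:

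1. Replace the concluding sentence of the margin rationale with one saying that 1.35 supports a difference from no therapy only on average, at the quoted point estimates, and not for mild patients considered alone.
2. Pre-specify SPT − PAP with a confidence interval in each AHI class, from a model with a therapy × AHI-class term.
3. State that a mild-subgroup result within 1.35 is not to be read as evidence of efficacy over no therapy.
4. Report, as supportive, an indirect estimate of SPT against no therapy (the quoted PAP effect minus the observed SPT − PAP, variances added), per class and for the observed mix.

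A formal success criterion at 0.68 in mild patients is not recommended. With 209 mild patients the observed difference would have to be below 0.68 − 1.971 × 0.277 = 0.13. Power would be about 0.8% at the assumed true difference of 0.8, and 69% even if SPT equalled PAP. Reimbursement statements should not be tied to such a criterion.

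The cost is a change of wording and a small supplementary analysis on a factor already used for stratification and subgrouping. The downside is a slightly weaker claim in mild patients.
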